### APPENDIX 3: Letter to GP – initial recruitment

Dear General Practitioner,

The Centre for Eye Research Australia (CERA) in collaboration with the Department of Optometry at the University of Melbourne are currently conducting a clinical trial examining the eye disease Age-related Macular Degeneration (AMD).

This study is a 3-year randomised controlled trial assessing the role of Simvastatin as a cholesterol-lowering medication, in the progression of early AMD. Participants in this study will receive an ophthalmic examination that includes photographs of the macular area. Participants enrolled in this study will be randomly assigned to the active or placebo arm of the trial. To take part in this study the participants must have lipid levels that are within a range that treatment is **not** recommended, as half will be on placebo.

Your patient has been identified by their ophthalmologist as having signs of AMD that fit our inclusion criteria and has shown interest in taking part in one of our research studies. We need to know what the fasting blood lipid levels are to determine which study they can take part in. Therefore, we would appreciate if you could organise for your patient to have their fasting cholesterol level assessed. (We require: total cholesterol level, HDL and LDL- cholesterol and triglyceride level). Or provide them with a copy of a recent test (within the last month) so that they can bring it to their initial study visit.

Should you require further information please feel free to contact me on [name] or [name].

Many thanks for your time and assistance.

[figure not shown]A handwritten signature in black ink, appearing to read '[name]', written in a cursive style.

[name]  
Head of Age-related Macular Degeneration Unit  
CERA.

**APPENDIX 6: Adverse event form**

|                                                                                                                                                    |
|----------------------------------------------------------------------------------------------------------------------------------------------------|
| 
ADVERSE EVENT FORM FOR CLINICAL STUDY:
“THE ROLE OF SIMVASTATIN IN EARLY AGE-RELATED MACULAR DEGENERATION”
 |
|----------------------------------------------------------------------------------------------------------------------------------------------------|

**PARTICIPANT ID NUMBER** \_\_\_\_\_ **DATE:** \_\_\_\_\_

**Description of symptoms:** \_\_\_\_\_

\_\_\_\_\_

\_\_\_\_\_

\_\_\_\_\_

\_\_\_\_\_

**Date symptoms commenced:** \_\_\_\_\_

**Date symptoms ceased:** \_\_\_\_\_

**Effect on study treatment:** \_\_\_\_\_

\_\_\_\_\_

**Was study treatment ceased permanently?**    **YES**            **NO**

**Follow-up required:**    **YES**            **NO**

**If YES outline follow-up required:** \_\_\_\_\_

\_\_\_\_\_

**Resolved no sequelae**            **Continuing**

## APPENDIX 7: ADVERSE EVENT FOLLOW-UP FORM

|                                                                                                                                 |
|---------------------------------------------------------------------------------------------------------------------------------|
| ADVERSE EVENT—FOLLOW-UP FORM FOR CLINICAL STUDY:
“THE ROLE OF SIMVASTATIN IN EARLY AGE-RELATED MACULAR DEGENERATION” |
|---------------------------------------------------------------------------------------------------------------------------------|

PARTICIPANT ID NUMBER \_\_\_\_\_ DATE: \_\_\_\_\_

Description of ongoing symptoms: \_\_\_\_\_

\_\_\_\_\_

\_\_\_\_\_

\_\_\_\_\_

\_\_\_\_\_

Date symptoms commenced: \_\_\_\_\_

Date symptoms ceased: \_\_\_\_\_

Effect on study treatment: \_\_\_\_\_

\_\_\_\_\_

Was study treatment ceased permanently?    YES            NO

Follow-up required:    YES            NO

If YES outline follow-up required: \_\_\_\_\_

\_\_\_\_\_

Resolved no sequelae            Continuing

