#### **11.4 Reporting and documentation of adverse events.**

At each visit, research staff will question all participants regarding any adverse experiences particularly muscle soreness as an indicator of possible rhabdomyolysis. Any illness, sign, symptom or clinically significant laboratory test abnormality that appear or worsen during the course of the clinical trial will be documented and pursued regardless of the causal relation to the active 'statin' therapy. Participants would also be encouraged to report any problems as they occur to the study centre where all details would be documented and upon the Chief Investigator's discretion further action would be recommended to the participant.

(Adverse Event form located in Appendix 5).

Laboratory blood analyses and repeat liver function test carried out after 4 weeks will allow the monitoring of changes in cholesterol levels as well as liver enzymes.

The safety issue of the study would be evaluated by a Safety Officer appointed to review all the reported incidents of adverse events between the two groups.

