## APPENDIX 9: Letter to GP on commencing medication

Dear doctor,

Your patient has been enrolled into the Age-Related Maculopathy Statins Study (ARMSS). This study looks at whether statin impacts on the rate of progression of age-related maculopathy (ARM). 50% of participants will be randomized to receive simvastatin 40mg, and 50% will be on an identical looking placebo.

Please be aware that simvastatin can have the following interactions drug interactions:

- Bile acid binding resins – reduce gastrointestinal absorption of statin. Give statin at least one hour before, or 4 hours after, bile acid binding resin.
- Clarithromycin, itraconazole, ketoconazole, erythromycin – increase risk of myopathy or rhabdomyolysis – stop statin temporarily, for the duration of antimicrobial treatment.
- Cyclosporin – increases risk of myopathy or rhabdomyolysis; use lowest effective statin dose, monitor for adverse effects, and measure creatinine kinase if indicated.
- Gemfibrozil – increases risk of myopathy and rhabdomyolysis; measure creatinine kinase 1 month after starting combined treatment with statin, then repeat at 6 month intervals and if symptoms of myopathy or rhabdomyolysis occur.
- Nicotinic acid (lipid lowering doses) – increases risk of myopathy and rhabdomyolysis; monitor clinically; measure creatinine kinase if indicated.
- Warfarin – statin may increase the INR and risk of bleeding; adjust warfarin dose according to INR.

Potential adverse effects:

- Common – myalgia, mild transient gastrointestinal symptoms, headache, insomnia, dizziness
- Rare – myopathy (with or without creatinine kinase elevation), rhabdomyolysis, renal failure, hepatitis, liver failure, alopecia, paraesthesia, peripheral neuropathy, impotence, nightmares, gynaecomastia, hypersensitivity, anaphylaxis, angioedema, toxic epidermal necrolysis, delayed wound healing
- Other – minor transient increases in transaminase and creatinine kinase are commonly found in the first weeks of treatment and appear to be dose related.

If there is any suspected side effect, or a clinical need to place your patient on a statin, or any of the medications mentioned above, we would very much appreciate you first contacting our chief investigator [name], or [name] on [name] before starting. Thank you for your cooperation.

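### The adverse event forms have no outcome code for death and no seriousness or severity field, so serious events can be separated by group only by classifying free text afterwards

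*Protocol*

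**What the plan says.** Section 11.4 sets a broad duty to record: "Any illness, sign, symptom or clinically significant laboratory test abnormality that appear or worsen during the course of the clinical trial will be documented", whatever the causal relation to the statin. It singles out muscle soreness as a pointer to possible rhabdomyolysis. It also appoints a Safety Officer to review the reported adverse events between the two groups.

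The instruments are in Appendices 6 and 7. The adverse event form has:

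- a multi-line field headed "Description of symptoms";
- dates on which symptoms began and ceased;
- a free-text field headed "Effect on study treatment";
- a yes/no item, "Was study treatment ceased permanently";
- a yes/no item on follow-up, with free text under "If YES outline follow-up required";
- two outcome boxes, "Resolved no sequelae" and continuing.

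The follow-up form repeats this layout, with the description field reworded for ongoing symptoms. It offers the same two outcomes.

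The GP letter in Appendix 9 lists rhabdomyolysis, renal failure, liver failure, anaphylaxis, toxic epidermal necrolysis and peripheral neuropathy among the rare adverse effects of simvastatin.

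**The concern.** The protocol names adverse effects that can end in death or lasting harm, yet its outcome item allows for neither explicitly. It also assigns a between-group safety review without collecting, in coded form, the two attributes on which such a review is normally organised: whether an event was serious and how severe it was.

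A statistical analysis plan can decide how to tabulate fields that exist. It cannot supply an attribute that was not recorded when the event occurred. If the free text does not say that a participant was admitted to hospital, or how bad the symptom was, that may not be recoverable later. At stake is the standard of the safety comparison, in particular whether serious events can be listed by group on criteria fixed in advance rather than by judgement applied afterwards.

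**Working it through.** No arithmetic in the protocol bears on this point and there is no stated figure to reproduce. The check sets each field of the two forms against what sections 11.3 and 11.4 and Appendix 9 say may happen and must be recorded.

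**1. What is coded.** Each form has three two-way items: permanent cessation, follow-up required, and outcome. That gives 2 × 2 × 2 = 8 possible coded patterns. None is reserved for a death, for lasting harm after resolution, for a serious event or for a severity grade. Everything else is dates or free text.

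**2. Hypothetical events run through the coded items.**

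| Event | Outcome box | Coded sign of seriousness or severity |
|---|---|---|
| Mild muscle soreness, drug ceased, settles | Resolved | None |
| Rhabdomyolysis with hospital admission, drug ceased, settles fully | Resolved | None |
| Event that settles but leaves a permanent deficit | No explicit box; continuing is the nearest | None |
| Fatal event | No valid box | None |

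If the follow-up item is answered alike, the first two rows give identical coded records and differ only in what someone writes in the description. In the third row, using the continuing box mixes residual damage with events still in progress. In the fourth, leaving both boxes empty makes a death look like an incomplete form.

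**3. What section 11.4 requires against what the form prompts for.** Section 11.4 covers illnesses, signs, symptoms and clinically significant laboratory abnormalities. The form's label and its two date fields refer to symptoms only. Section 11.3 lists raised creatine kinase and transaminases among the reported effects of simvastatin, and these may produce no symptom to describe or date. Staff can still write them in, so this is a mismatch of wording and not a bar to recording.

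**4. Whether the attribute is defined elsewhere.** The protocol text shown contains no definition of a serious adverse event, no severity scale and no rule by which the Safety Officer would classify free text.

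**The case against.** The strongest reply is that the forms capture more than their tick boxes. An event such as liver failure would be written by name, with dates, its effect on treatment and the follow-up planned. Section 11.4 asks the Safety Officer only to review reported incidents between groups, and named events and permanent cessations permit that. The forms are also not the only safety source: Appendix 10 schedules fasting blood, medical history and a medication list at every visit, and side-effect reporting at every visit after the first. Section 11.4 has problems reported to the centre documented there as well. All of this stands. A reader might infer that serious events cannot be recorded or compared at all, and the documents do not support that.

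Three further inferences are tempting and also fail.

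- **Temporary stops.** Appendix 9 tells GPs to "stop statin temporarily, for the duration of antimicrobial treatment", while the form codes only permanent cessation. A pause for an interacting drug is not an adverse event, medications are listed at every visit, and section 7 has unused tablets returned to assess compliance. A pause caused by an adverse event can be entered under "Effect on study treatment".
- **Serious events lost among mild ones.** Section 11.3 quotes mild effects at between 2% and 8%. Multiplying these by the arm size gives a count of expected mild reports. It does not measure how many serious events would be missed.
- **Lasting harm has nowhere to go.** The continuing box, with a description on the follow-up form, is a workable if ambiguous home. Only death has no valid code.

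A serious-event reporting procedure may also exist outside the protocol. None is shown, and the printed forms do not refer to one.

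**Conclusion.** The point holds in a limited form. The outcome item has no valid code for a fatal event and no explicit code for resolution with sequelae. Because neither form codes seriousness or severity, the groups can be compared on those attributes only by classifying free text afterwards.

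The size is two missing outcome options and two uncoded attributes on each of two forms. It cannot be expressed as a number of events lost, and it does not touch the efficacy analysis or the sample size. It is an inexpensive improvement to the safety data and does not by itself invalidate the safety review.

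The conclusion assumes that the forms as printed are those used and that no separate serious-event form exists. If one does, the protocol should refer to it and the gap narrows accordingly.

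**What to change.** On both forms in Appendices 6 and 7:

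1. Add two outcome options: resolved with sequelae, and fatal.
2. Add a coded seriousness item (yes/no, with the criterion met) and a coded severity item, and define both in section 11.4.
3. Relabel the description field so that it names all four kinds of finding in section 11.4 (illnesses, signs, symptoms and laboratory abnormalities), and word the date fields to match.

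In section 11.4, state that the Safety Officer reviews serious events by group separately from the rest. Its pointer to Appendix 5 for the form can be corrected at the same time, since the contents list and the form itself say Appendix 6.

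The cost is a revised one-page form, a few added database fields, and a minute or two more per event. It needs no extra visits or staff.

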## **APPENDIX 8: Letter to participant on commencing medication**

The study medication is either simvastatin, at a dose of 40mg, or placebo.

### **Instruction**

Take two tablets in the evening with food. Avoid drinking grapefruit juice within 4 hours of taking the medication as this may interfere with absorption.

Severe side effects are rare, but seek medical advice promptly if you experience muscle pain, tenderness or weakness, dark urine, or yellowing of skin or the whites of your eyes.

**Please give the enclosed “information for GP” to your local doctor. Please remind him/her that you are now in this trial, especially when he is about to prescribe any drug (particularly antibiotics), as there are a few but important interactions.**

Please call [name] on [name], or [name] on [name] if you have any questions regarding the medication or the trial.

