#### 4. STUDY OBJECTIVES

**The primary objective** of this study is to determine whether SIMVASTATIN at 40mg per day versus a placebo affects the progression of early AMD, either to the development of late stage AMD, defined as either CNV or central geographic atrophy, or as worsening macular status within the stage of early AMD.

**Secondary objectives** are to measure changes in visual function results over time and to determine how the genotype influences the findings on AMD progression in normocholesterolaemic participants.

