## **7. STUDY MEDICATIONS**

**Dose:** The medication involved in this study are either SIMVASTATIN at 40mg per tablet or a PLACEBO.

Both are supplied by Merck Sharp & Dolme Pty Ltd.

**Administration:** Patients receive their study medication following the completion of their baseline assessment.

Unused tablets and empty jars are requested to be returned to the study centre for assessment of compliance.

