## **8.5 Allocation of randomised study treatment**

Once participants have completed all baseline assessments they receive either simvastatin 40mg or placebo. For tracking, each participant is allocated a study medication number which is to be recorded in the database as well as a log book. Each medication number will correspond to either active medication or placebo, which is unknown to the participant and the study team. Participants will keep the same medication number for the duration of their participation in the study.

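### Tablet strength (40 mg), tablet count (two each evening) and daily dose (40 mg) cannot all be right: strength times count is 80 mg

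*Protocol*

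**What the plan says.** Three quantities fix the daily dose, and the protocol states all three.

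- **Daily dose.** Section 4 gives "SIMVASTATIN at 40mg per day versus a placebo". The opening line of Appendix 8 agrees: "The study medication is either simvastatin, at a dose of 40mg, or placebo". Section 8.5 ("they receive either simvastatin 40mg or placebo") and the GP letter in Appendix 9 ("50% of participants will be randomized to receive simvastatin 40mg") also give 40 mg, without saying whether that is per day or per tablet.
- **Tablet strength.** Section 7, under the label for dose, gives "either SIMVASTATIN at 40mg per tablet or a PLACEBO". No other section states a strength.
- **Tablets per day.** Appendix 8 instructs participants: "Take two tablets in the evening with food". No other section states a count.

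Section 7 also asks for unused tablets to be returned so that compliance can be assessed. Section 11.3 introduces its list of side effects by reference to earlier studies using doses up to 40 mg.

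**The concern.** Read together, section 7 and Appendix 8 give a daily dose that differs from the one in the objective. The participant letter is a direct dosing instruction, so what a participant takes should not depend on which section is believed.

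Three things are at stake if the tablets are 40 mg and the letter is followed:

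- Participants on active drug take twice the intended dose, above the range for which section 11.3 describes side effects.
- Their GPs have been told 40 mg, in a letter where dose matters. For cyclosporin it advises "use lowest effective statin dose, monitor for adverse effects", and it notes that "minor transient increases in transaminase and creatinine kinase are commonly found in the first weeks of treatment and appear to be dose related".
- Masked staff would not notice from the instructions, because the arms have identical-looking tablets and no separate letter is described for each arm.

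One consequence holds whichever figure is wrong. The expected tablet use per day is either one or two, depending on the section consulted, so compliance from returned tablets has no settled denominator.

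**Working it through.** **Inputs**

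- Dose D = 40 mg per day (section 4; Appendix 8 also states a 40 mg dose)
- Strength S = 40 mg per tablet (section 7)
- Count N = 2 tablets per day (Appendix 8)

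**Formula:** D = S × N.

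**The plan's own figure.** The stated 40 mg per day is not reproduced: 40 × 2 = 80 mg per day. The ratio to plan is 80 / 40 = 2.0 and the excess is 80 − 40 = 40 mg.

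**Each pair against the third figure**

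| Taken as correct | Implies | Protocol states |
|---|---|---|
| Strength and count | D = 40 × 2 = 80 mg per day | 40 mg per day |
| Strength and dose | N = 40 / 40 = 1 tablet | 2 tablets |
| Count and dose | S = 40 / 2 = 20 mg per tablet | 40 mg per tablet |

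Every pair contradicts the remaining figure.

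**What participants on active drug would take**

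| Reading | Daily dose | Ratio to plan |
|---|---|---|
| 20 mg tablets (assumption), two taken | 20 × 2 = 40 mg | 1.0 |
| 40 mg tablets, letter followed as written | 40 × 2 = 80 mg | 2.0 |
| 40 mg tablets, letter corrected to one | 40 × 1 = 40 mg | 1.0 |

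**Ways the three might be reconciled.** One active and one placebo tablet each evening would also give 40 mg, but the protocol describes no such scheme and section 7 presents the medication as one or the other. The text reviewed mentions no 20 mg tablet, titration or 80 mg dose. The consent and participant information appendices and the text between sections 2 and 4 were not available for this check. They might show which figure is right, but they cannot make all three true.

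**Compliance.** If a participant uses n tablets over d days, apparent compliance is n / d when one a day is expected and n / (2d) when two are expected. The same returns therefore give values that differ by a factor of 2.

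**The case against.** The strongest reply is that the harmless reading is the more natural one. Appendix 8 is coherent by itself: it states a 40 mg dose and, directly below, two tablets, which together imply 20 mg tablets. The odd words are *per tablet* in section 7, which stand under a label for dose and may be loose drafting. On that reading participants take exactly what was planned. This may well be what happened, but it rests on a strength that the protocol never states, and section 7 would still misdescribe the product.

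Some supporting points deserve less weight than the contradiction itself:

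- Section 11.3 describes past use up to 40 mg. It does not set a maximum.
- Section 8.5 and Appendix 9 give 40 mg without a unit of time or tablet, so they fit a strength as well as a daily dose. Only section 4 and the opening of Appendix 8 clearly speak of a dose.
- Appendix 9 asks GPs to contact the study team before starting the interacting drugs, so they are not meant to act on the 40 mg figure alone.
- The labels on the tablet jars may carry their own directions; the protocol does not say.

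Safeguards would also limit harm: the ALT exclusion (section 6.3), liver tests at 4 weeks and questions about muscle soreness at each visit (section 11.4), fasting blood at every visit (Appendix 10), and the symptom warning in the participant letter. These help to detect or limit harm. They do not settle the tablet strength.

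**Conclusion.** The concern holds. Stated strength times stated count is 80 mg, against a stated dose of 40 mg, so at least one figure is wrong. That conclusion uses only the protocol's own numbers and is firm.

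Which figure is wrong is not known. The 40 mg daily dose is the best supported, so the error is probably in the strength (section 7) or the count (Appendix 8). If it is the strength, actual dosing is 1.0 times plan, assuming 20 mg tablets. If it is the count, participants on active drug who follow the letter take 2.0 times plan.

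No claim is made that anyone took 80 mg, or about how many might have. Sample size and the randomised, masked comparison are unaffected. It still has to be corrected, because a possible twofold dosing error in a participant instruction should not be left to inference.

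**What to change.** Check the tablet strength against the supply record before any further Appendix 8 letter is issued. Then:

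- **If tablets are 20 mg:** correct section 7 to 20 mg per tablet, two tablets once daily (40 mg), with two matching placebo tablets. Leave Appendices 8 and 9 as they are.
- **If tablets are 40 mg:** change the Appendix 8 instruction to one tablet each evening with food, send the correction to participants and their GPs in both arms alike so that masking holds, and inform the Safety Officer.
- **In either case:** state the confirmed tablets per day in section 7 and use that number when assessing returned tablets.

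The cost is one check of the supply record, a one-line correction to section 7 or Appendix 8, and the tablets-per-day figure in section 7. Correction letters are needed only if the tablets are 40 mg.
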